## Other Data Collection

We will track patient attendance at study classes for both groups and compliance with home Tai Chi practice for the Tai Chi group. The Study Nurse will also monitor patients blood pressure and heart rate immediately before and after class at baseline, 6, and 12 weeks.

To keep track of patients’ level of physical activity outside of Tai Chi sessions, we will use the CHAMPS Physical Activity Questionnaire.98

## Qualitative Interviews

In a subset of 30-35 patients, we will also perform semi-structured qualitative exit interviews to further explore areas not captured in our standardized quantitative instruments. Particularly, we will be interested in patients’ candid assessments (positive, negative, and neutral) of various aspects of the Tai Chi intervention. These open-ended questions may yield additional insights into understanding mechanism of a mind-body exercise program and to further explore the relationships between beliefs, attitudes, and expectations. Interviews in the control group participants will also give comparative information regarding the education-attention control. One-hour exit interviews will be conducted at the end of the study by a study nurse or investigator and will be audiotaped. These audiotapes will be transcribed verbatim to provide transcripts of the interviews, which will be used for qualitative analyses. The transcripts will be reviewed in conjunction with the taped interview to ensure accuracy and the data will be analyzed. The audiotapes and transcripts will be kept in a locked cabinet in the research assistant’s locked office until all transcription and reviews have been performed. The audiotape will not be duplicated, distributed, or used for any purpose other than those described in this study. Once the investigators are satisfied that the data accurately reflects the taped interview, the audiotapes will be destroyed.

## 2. STATISTICAL CONSIDERATIONS

### Sample Size Justification

We will enroll a total of 100 patients, with 50 patients in each group. We estimate that 75 of patients will be enrolled from BIDMC and 25 patients from other study sites (eg. BWH and MGH).

The sample size is based on power calculations using data from our pilot study. For these calculations, we assumed a 1) 10% loss of efficiency because we will use non-parametric tests and 2) 20% dropout rate. Although all patients enrolled in the pilot study completed that study, we did have a few missing data points. Therefore we felt it would be prudent to anticipate a larger dropout rate given prior experiences with HF patients.

Since there are three primary endpoints (change in six-minute walk, peak VO2, MLHF score), we will apply a Bonferroni adjustment to preserve the 5% level of significance. Based on pilot data, the standard deviation (SD) for change in walk test distance=317 feet; SD for change in peak VO2=2.1 ml/kg/min; and SD for change in MLHF score=17 points. Accounting for the above, the sample of 50 patients per group provides 80% power to detect a peak VO2 difference of 1.5 ml/kg/min between groups. We will have >90% power to detect a walk test difference of 240 ft and 83% power to detect MLHF score difference of 12.5 between groups, each of which is half the magnitude of difference observed in the pilot study. These differences represent clinically meaningful changes in functional capacity and quality of life.

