### Analysis Plan for Primary Specific Aims

To assess the adequacy of randomization, we will use Fisher’s Exact tests (categorical variables, e.g., sex, NYHA Class) and Wilcoxon rank-sum tests (continuous variables, e.g., age) to detect any differences in baseline characteristics between treatment groups.

Our three primary endpoints are change in exercise capacity and quality of life from baseline to 12 weeks using the six-minute walk, peak VO2 and MLHF score. Because we will recruit patients from 3 institutions, we will formally examine whether there is a site effect by performing Kruskall-Wallis tests to assess whether changes from baseline to 12 weeks differ by site for each outcome. In the event that we observe a site effect, we will proceed stratifying our analyses by site using van Elteren’s test. A priori, however, we do not expect to observe a site effect for a number of reasons, including the 3 institutions are academic tertiary care centers located in the same catchment area, they have similar patient profiles, and they apply the same standard of cardiac care by following ACC/AHA guideline. If no site effect is observed, we will proceed with our analyses by performing two-sample non-parametric Wilcoxon rank-sum tests to compare the distribution of change from baseline to 12 weeks between treatment and control groups for each outcome measure.

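### Bonferroni for the three primary endpoints is valid, but Holm's step-down procedure keeps the same 5% familywise error and gains power when more than one effect is real

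*Protocol*

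**What the plan says.** The protocol's Sample Size Justification gives the reason for adjusting, "Since there are three primary endpoints (change in six-minute walk, peak VO2, MLHF score"), and then the method: "we will apply a Bonferroni adjustment to preserve the 5% level of significance". It plans "We will enroll a total of 100 patients, with 50 patients in each group", allows for a "10% loss of efficiency because we will use non-parametric tests" and a "20% dropout rate", and states power after these allowances for a planned difference on each of the three endpoints.

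The Analysis Plan for Primary Specific Aims names the same family, "Our three primary endpoints are change in exercise capacity and quality of life from baseline to 12 weeks", and tests each endpoint with "two-sample non-parametric Wilcoxon rank-sum tests to compare the distribution of change from baseline to 12 weeks between treatment and control groups", or with van Elteren's test if a site effect is seen. That section gives no significance threshold and no testing order, so the sentence in the sample size section is the only multiplicity rule in the protocol.

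**The concern.** Under plain Bonferroni every endpoint is judged at 0.0167, whatever the other two show. Holm judges the smallest p-value at 0.05/3 = 0.0167. If that is rejected, it judges the next at 0.05/2 = 0.025, and if that is also rejected, the last at 0.05. It stops at the first failure.

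Bonferroni gives up most when several effects are real. That is this trial's planning scenario, because the protocol powers all three endpoints on expected differences. At stake is power on the second and third endpoints to be declared, in a trial limited to 100 patients. Error control is not at stake, nor is the chance of finding at least one effect.

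**Working it through.** **Inputs from the Sample Size Justification.** 50 per arm, 20% dropout, 10% efficiency loss, three endpoints, familywise 5%. Planned difference and SD of change: VO2 1.5 and 2.1 ml/kg/min; walk 240 and 317 ft; MLHF 12.5 and 17 points.

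**Assumptions, because the protocol gives neither.** Two-sided tests; equal correlation between the endpoints, varied from 0 to 0.8.

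**Step 1. Does Bonferroni do what the protocol says?** Yes. 3 × 0.01667 = 0.05 is an upper bound under any correlation, and with independent endpoints the error is 1 − (1 − 0.01667)³ = 0.0492.

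**Step 2. The protocol's own power figures.** It states 80% (VO2), above 90% (walk) and 83% (MLHF). With both allowances, effective n = 50 × 0.8 × 0.9 = 36 per arm. Normal approximation: power = Φ(δ/σ × √(n/2) − z), with z = 2.394 for two-sided 0.0167 and √18 = 4.243.
- VO2: 0.714 × 4.243 = 3.030; Φ(0.636) = 73.8%
- Walk: 0.757 × 4.243 = 3.212; Φ(0.818) = 79.3%
- MLHF: 0.735 × 4.243 = 3.120; Φ(0.726) = 76.6%

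The stated figures are not reproduced at n = 36. Reading dropout as 50/1.2 = 41.7 per arm, with no efficiency loss, gives 80.7/85.6/83.2% for VO2/walk/MLHF. That matches VO2 and MLHF but not walk. The baseline therefore depends on how the allowances are read, and Step 4 uses several readings.

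**Step 3. Is Holm's error control the same?** Suppose m of the three null hypotheses are true. When Holm first comes to a true null, all m true nulls are still untested, so the threshold is at most 0.05/m. A false rejection therefore needs some true null to have p ≤ 0.05/m, which has probability at most m × 0.05/m = 0.05 under any correlation. Holm's thresholds are never below 0.0167, so it rejects everything that Bonferroni rejects.

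Simulated familywise error when all three nulls are true is identical for the two methods: 4.9% at correlation 0 and 4.8% at 0.3.

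**Step 4. Power, Bonferroni to Holm.** Trivariate normal simulation with means δ/σ × √(n/2), all three planned effects real:

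| n per arm | Correlation | VO2 | Walk | MLHF |
|---|---|---|---|---|
| 36 | 0 | 74 to 83% | 79 to 87% | 77 to 85% |
| 36 | 0.3 | 74 to 82% | 79 to 86% | 77 to 84% |
| 36 | 0.6 | 74 to 81% | 79 to 85% | 77 to 83% |
| 36 | 0.8 | 74 to 81% | 79 to 84% | 77 to 82% |
| 40 | 0.3 | 79 to 87% | 84 to 90% | 81 to 88% |
| 41.7 | 0.3 | 81 to 88% | 86 to 91% | 83 to 90% |

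At n = 36 the gain per endpoint is 4 to 9 points over correlations 0 to 0.8. The chance that all three are significant rises from 51% to 70% at correlation 0.3.

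**Step 5. Where the gain is small or absent** (n = 36, correlation 0.3).
- At least one endpoint significant, all three effects real: 96.1% under both methods, because the smallest p-value meets the same threshold.
- Only VO2 and MLHF real: about 3 points on each.
- Only VO2 real: 73.9% to 74.0%. Each of the two null endpoints is then rejected in about 2.4% of trials instead of 1.7%, still inside the 5% familywise limit.

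**The case against.** The strongest reply is that nothing here is wrong. Bonferroni is valid and prespecified, meets the purpose the protocol gives for it, and is conflicted with by no other section. All of that stands, so the point can only be an improvement. It is still more than a preference between equals, because Holm needs no extra assumption and loses no rejection.

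Three stronger readings are tempting, and the protocol does not support them.
- A reader might infer that Holm always has more power. It does not: the chance of at least one rejection is the same, and with a single real effect the gain is practically nil.
- A reader might infer that Bonferroni pushes every endpoint below 80% power and that Holm repairs this. The values below 80% appear because the stated powers do not reproduce when both allowances are applied. That is a separate issue. At 41.7 per arm Bonferroni gives 81/86/83%, and Holm still adds about 5 to 7 points.
- A reader might take the rise from 51% to 70% as the trial's chance of success. The protocol does not require all three endpoints to be significant.

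A practical objection also stands. Bonferroni has matching 98.3% simultaneous intervals. Under Holm, an endpoint rejected at the second or third step, say with p = 0.03 at the last step, can have a 98.3% interval that includes no difference. Power under Holm also depends on correlations the protocol does not have, which is a good reason to leave the sample size at the single-step level.

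The statistical analysis plan is not at hand and may already set out a testing procedure. If it names Holm, the protocol sentence only needs to be brought into line.

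**Conclusion.** The point holds as an efficiency improvement. With 36 effective patients per arm, two-sided tests and an assumed correlation of 0.3, Holm raises per-endpoint power by about 7 to 9 points if all three planned effects are real. It leaves the chance of at least one significant endpoint unchanged.

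The comparison rests on the protocol's pilot SDs and planned differences, a normal approximation to the rank-sum tests, and a correlation the protocol does not give. The direction of the result depends on none of these. The size of the gain depends mainly on how many effects are real, and less on the correlation or on how the dropout and efficiency allowances are read.

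**What to change.** Before outcome data are seen:
- In the Sample Size Justification, replace the Bonferroni adjustment with the Holm step-down procedure at familywise two-sided 5%.
- In the Analysis Plan for Primary Specific Aims, apply it to the p-values of the three primary tests, rank-sum or van Elteren as the case may be.
- Keep the sample size calculation at 0.0167 per endpoint and say that this is conservative, so that no correlation has to be assumed.
- State that significance is decided by the Holm-adjusted p-values. Report 98.3% intervals alongside, with a note that they can include no difference for an endpoint rejected at a later step.

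The cost is a sentence or two in each section. No endpoint, test or patient number changes.

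### The >90% power stated for the six-minute walk does not follow from the protocol's own inputs and cannot stand beside the 80% and 83% stated for peak VO2 and MLHF

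*Protocol*

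**What the plan says.** The Protocol's Sample Size Justification (section 2, Statistical Considerations) gives almost all the inputs in one place.

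- Size: "We will enroll a total of 100 patients, with 50 patients in each group".
- Allowances: "10% loss of efficiency because we will use non-parametric tests and 2) 20% dropout rate".
- Multiplicity: with three primary endpoints, "we will apply a Bonferroni adjustment to preserve the 5% level of significance".
- Variability, from the pilot: "the standard deviation (SD) for change in walk test distance=317 feet"; "SD for change in peak VO2=2.1 ml/kg/min"; and 17 points for the change in MLHF score.
- Results, said to take all of this into account: "the sample of 50 patients per group provides 80% power to detect a peak VO2 difference of 1.5 ml/kg/min between groups"; and "We will have >90% power to detect a walk test difference of 240 ft and 83% power to detect MLHF score difference of 12.5".

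The Analysis Plan for Primary Specific Aims names a two-sample Wilcoxon rank-sum test on the change from baseline to 12 weeks for each endpoint. Neither section says whether the tests are one-sided or two-sided.

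**The concern.** The three endpoints share one sample size, one dropout rate, one efficiency allowance and one per-test alpha, so their powers can differ only through the ratio of difference to SD. Those ratios are close together, yet the stated powers run from 80% to above 90%. At least one figure must come from a different calculation.

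This paragraph is the whole justification for 100 patients and covers every primary endpoint. For the walk test it puts the chance of missing a true 240 ft difference below 10%. If the real chance is 14 to 21%, a reader of a null walk result would give it more weight than the design supports.

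**Working it through.** **Inputs** (all from the Sample Size Justification)

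- Effective number per group: n = 50 × 0.8 × 0.9 = 36.
- Per-test alpha: 0.05/3 = 0.0167. The critical value is 2.394 two-sided and 2.128 one-sided.
- Standardised differences d: VO2 1.5/2.1 = 0.714; MLHF 12.5/17 = 0.735; walk 240/317 = 0.757.

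**Formula.** Power = Φ(d√(n/2) − z), where z is the critical value. This was checked against the noncentral t distribution.

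**Step 1: try to reproduce the stated figures with every allowance kept.** At n = 36, √(n/2) = 4.243, so d√(n/2) is 3.030 (VO2), 3.212 (walk) and 3.120 (MLHF).

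| Per-test alpha | VO2 | Walk | MLHF |
|---|---|---|---|
| Stated in the protocol | 80% | >90% | 83% |
| 0.0167 two-sided, normal | Φ(0.636) = 73.8% | Φ(0.818) = 79.3% | Φ(0.726) = 76.6% |
| 0.0167 two-sided, noncentral t | 71.7% | 77.4% | 74.6% |
| 0.0167 one-sided, normal | Φ(0.902) = 81.7% | Φ(1.084) = 86.1% | Φ(0.992) = 83.9% |
| 0.0167 one-sided, noncentral t | 80.3% | 84.9% | 82.7% |

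The one-sided noncentral t row rounds to the stated 80% and 83%. No row gives more than 90% for the walk.

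**Step 2: check the three figures against each other, without fixing n.** If VO2 has 80% power, then d√(n/2) for VO2 equals z + 0.842. The walk value is larger by the factor 0.757/0.714 = 1.060.

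- Two-sided 0.0167: (2.394 + 0.842) × 1.060 − 2.394 = 1.036, giving 85.0%.
- One-sided 0.0167: (2.128 + 0.842) × 1.060 − 2.128 = 1.020, giving 84.6%.
- Two-sided 0.05, no Bonferroni: (1.960 + 0.842) × 1.060 − 1.960 = 1.010, giving 84.4%.

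The same step for MLHF (factor 0.735/0.714 = 1.029) gives 82 to 83%, which agrees with the stated 83%. So VO2 and MLHF are consistent with each other, and the walk figure is the one that does not fit. This holds whatever the sidedness and whatever allowances were applied.

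**Step 3: see what would lift the walk above 90%.** With two-sided 0.0167, walk power is 83.9% at n = 40 (dropout only), 88.4% at n = 45 (efficiency loss only) and 91.8% at n = 50 (neither). With two-sided 0.05 and no Bonferroni, n = 36 gives 89.5%. With one-sided 0.0167, 90% needs about 41 effective per group (42 with noncentral t), against 36 available. In each case the figure passes 90% only if at least one stated adjustment is relaxed.

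**Step 4: find the detectable differences if the tests are two-sided (normal approximation).** At 80% power, d = (2.394 + 0.842) × √(2/36) = 0.763. That is 0.763 × 2.1 = 1.60 ml/kg/min, 0.763 × 317 = 242 ft and 0.763 × 17 = 13.0 points. For 90% power on the walk, (2.394 + 1.282) × √(2/36) × 317 = 275 ft, against the stated 240 ft.

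**The case against.** The best defence is that sidedness is not stated. With a one-sided per-test alpha of 0.0167 and every allowance kept, the noncentral t gives 80.3% for VO2 and 82.7% for MLHF, which are the protocol's figures after rounding. That stands. A reader who computes only the two-sided powers might infer that none of the three figures follows from the inputs, or that power is overstated for all three endpoints. The document does not support either inference, because two-sided testing is the reader's assumption. Nor does anything in it point to one-sided testing: it speaks of differences between groups and of comparing distributions, with no direction given.

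A reader might also infer which allowance was left out of which figure. That would be guesswork. Under a two-sided test, dropout alone gives 78.8% and 81.4% for VO2 and MLHF, and efficiency loss alone gives 84.0% and 86.3%. Neither pair matches 80% and 83%.

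Finally, the practical size is modest. Even two-sided, the walk test has about 79% power for 240 ft. The detectable differences at 80% power exceed the stated ones by about 7% (VO2), under 1% (walk) and 4% (MLHF), and the SDs come from a pilot of 30 patients. This also stands, and it means the point is no argument for a larger trial. It does not rescue the >90%, which fails on either reading.

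**Conclusion.** The point holds for the walk test without any assumption about sidedness. The stated >90% is not obtainable from the stated inputs, and it conflicts with the 80% and 83% given beside it. The figure consistent with those two is about 85%, so the chance of missing a 240 ft difference is about 15%, not under 10%.

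For VO2 and MLHF the conclusion is conditional. The stated powers are right if the tests are one-sided at 0.0167. If the tests are two-sided, the stated powers are about 6 points too high, and all three become about 74% (VO2), 79% (walk) and 77% (MLHF), or 72%, 77% and 75% with noncentral t. The chance of missing the walk difference is then about 21%.

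These results take the pilot SDs as given and apply dropout and efficiency loss multiplicatively to 50 per group.

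**What to change.** In the Sample Size Justification, state whether the tests are one-sided or two-sided and give the per-test alpha. Recompute all three powers from that single set of inputs, and withdraw >90% for the walk test.

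- If two-sided: state about 74% for 1.5 ml/kg/min, 79% for 240 ft and 77% for 12.5 points, labelled as two-sided. Alternatively, keep 80% power and quote detectable differences of about 1.60 ml/kg/min, 242 ft and 13.0 points.
- If one-sided: say so, keep 80% and 83%, and state about 85% for the walk.

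The cost is a change of protocol wording and a less favourable stated power. The sample size and the planned tests stay as they are.

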### Statistical Analysis and Power

Prior to analyzing the outcomes, we will compare the randomized groups with respect to baseline demographic, functional, and clinical variables as well as known prognostic factors (such as baseline NYHA class and baseline peak VO2) using chi-square and Fisher’s exact tests. Although we do not expect any differences with proper randomization, any significant imbalances (p<.05) will be adjusted for in the statistical analyses. All analyses will be performed on an intention-to-treat basis.

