## Subject Selection

The sample will be identified from the ambulatory clinics at three main institutions: Beth Israel Deaconess Medical Center (BIDMC), Brigham and Women’s Hospital (BWH), and Massachusetts General Hospital (MGH). In addition to the two advanced HF specialty clinics (BIDMC and BWH) utilized in our pilot, we will also be recruiting from the primary care and cardiology clinics at each of the hospitals and affiliated community practices. The HF clinics combined see approximately 4000 patients per year. For our pilot study, we were able to enroll 30 patients over 1 year from two clinics with very minimal recruiting resources.

Hebrew Senior Life (HSL): We will also recruit eligible subjects from Hebrew Senior Life in Roslindale and two community housing facilities associated with HSL: Jack Satter House in Revere and the Simon Fireman Community in Randolph.

Most sites are concentrated in the same 3-block radius on the Harvard Longwood Medical Campus. The MGH is located approximately 3 miles from Longwood with a shuttle bus available between sites every 15 minutes. In addition, we will advertise the study via newspapers and flyers.

As HF is primarily a disease of the elderly, we expect to have mainly a population >60 years of age. We do not expect to have many patients below the age of 30, although this is theoretically possible with entities such as peripartum cardiomyopathy. Based upon our pilot data, we expect that more than 50% of patients will be ≥65 years of age, and over 80% will be ≥55. Patients will be excluded if they cannot safely complete the necessary testing measurements (such as exercise stress testing). We will recruit both men and women, as well as participants of all races and ethnicities.

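### A p<.05 baseline test decides whether and for what the primary endpoints are adjusted, which leaves the primary analysis open and gives up precision; the site pre-test is a minor companion problem

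*Protocol*

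**What the plan says.** **Baseline rule (Statistical Analysis and Power).** Before outcomes are analysed, the arms are compared on "baseline demographic, functional, and clinical variables as well as known prognostic factors (such as baseline NYHA class and baseline peak VO2"). This screening is to be done "using chi-square and Fisher’s exact tests". Then "any significant imbalances (p<.05) will be adjusted for in the statistical analyses". The section says that no differences are expected if randomisation is done properly. It gives no closed list of variables and no method of adjustment.

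**Primary test (Analysis Plan for Primary Specific Aims).** Change from baseline to 12 weeks in six-minute walk, peak VO2 and MLHF score is compared by two-sample Wilcoxon rank-sum tests. The same section describes the baseline comparison differently: "we will use Fisher’s Exact tests (categorical variables, e.g., sex, NYHA Class) and Wilcoxon rank-sum tests (continuous variables, e.g., age").

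**Site rule (same section).** The plan is "performing Kruskall-Wallis tests to assess whether changes from baseline to 12 weeks differ by site for each outcome". The result of that test then selects the primary method: "In the event that we observe a site effect, we will proceed stratifying our analyses by site using van Elteren’s test"; otherwise the unstratified Wilcoxon test is used. No significance level defines when a site effect counts as observed. The reasoning rests on three academic tertiary centres.

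**Related text.** Subject Selection adds a fourth source: "We will also recruit eligible subjects from Hebrew Senior Life in Roslindale and two community housing facilities associated with HSL". Under Procedures for obtaining Informed Consent, randomisation is stratified by NYHA class (I/II versus III) and not by site. Sample Size Justification allows a 10% efficiency loss for non-parametric tests and 20% dropout, with a Bonferroni adjustment over the three endpoints.

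**The concern.** After proper randomisation, every imbalance at p<.05 is a chance event. The p-value depends on sample size and luck. It does not show whether the variable predicts the outcome. A strong predictor with p=0.10 would go unadjusted, while an irrelevant variable with p=0.04 would be adjusted for.

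The rule also has no defined end point. When it fires, the Wilcoxon test has to give way to something that can hold a covariate, and the Protocol does not say what. Even the screening step is described in two ways. The tests named under Statistical Analysis and Power are for categorical data and do not suit peak VO2, which that section itself lists.

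Two things are at stake. The primary analysis cannot be stated before the baseline data are in. And the precision available from known predictors, first of all the endpoint's own baseline value, is collected only when chance happens to flag them.

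The site rule is a smaller matter of the same kind. It can give the three primary endpoints different tests, and it does not say to which site a Hebrew Senior Life patient belongs.

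**Working it through.** **1. Inputs from the Protocol.** 50 per arm; 20% dropout, so 50 × 0.8 = 40 per arm evaluable; three endpoints, so α = 0.05/3 = 0.0167 each; peak VO2 SD of change 2.1 and difference 1.5; enrolment of 75 from BIDMC and 25 from other sites. A two-sided test is assumed, as the Protocol does not state sidedness.

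**2. The plan's own figure.** The Protocol states 80% power for peak VO2.
- Standardised difference: 1.5/2.1 = 0.714.
- Noncentrality at 40 per arm: 0.714 × √(40/2) = 3.194.
- Critical value at two-sided 0.0167: 2.394.
- Power = Φ(3.194 − 2.394) = 78.8%, close to the stated 80%. With the 10% efficiency loss as well (36 per arm) it is 73.8%.

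**3. How often the baseline rule fires by chance.** For k independent variables the chance of at least one p<.05 is 1 − 0.95^k. The Protocol names four variables (NYHA class, peak VO2, sex, age) within an open list, so k is an assumption.

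| k | Chance of at least one trigger |
|---|---|
| 4 | 18.5% |
| 10 | 40.1% |
| 15 | 53.7% |
| 20 | 64.2% |

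With an assumed pairwise correlation of 0.3 to 0.5, simulation gives 16-17% for 4 variables and 36-45% for 15. Stratifying on NYHA class lowers the figures further. Any single prognostic variable is flagged only about 5% of the time.

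**4. What the rule costs in power.** Pre-specified adjustment for a covariate with correlation r to the 12-week change divides the residual SD by a factor that raises the noncentrality to 3.194/√(1 − r²).
- r = 0.3: 3.194/0.954 = 3.35; Φ(3.35 − 2.394) = 83%.
- r = 0.5: 3.194/0.866 = 3.69; Φ(3.69 − 2.394) = 90%.

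These normal approximations run slightly high. Simulation with 40 per arm gives 82-88% over that range for pre-specified adjustment, against about 75-76% under the imbalance rule. A separate simulation at r = 0.5 gave about 74-75% against 88-89%. A small part of the gap comes from using a parametric test: with r = 0, ANCOVA gave about 76% and Wilcoxon about 75%.

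**5. Type I error of the baseline rule.** At nominal 0.0167 the simulated rate was 0.010 to 0.016. It turns conservative when the flagged variable is prognostic.

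**6. Site rule.** Expected completers: 75 × 0.8 = 60 from BIDMC and 25 × 0.8 = 20 elsewhere. A 60/10/10 split and a 0.05 threshold are assumed.

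| True shift at one small site | Kruskal-Wallis rejects |
|---|---|
| none | 4.6% |
| 0.5 SD | 22% |
| 0.8 SD | 50% |

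Over three independent endpoints the chance of a false trigger is 1 − 0.95³ = 14.3%. Simulated type I error of the full site rule was 0.0150 to 0.0182. Its verdict differed from that of a fixed Wilcoxon test in 0.04-0.8% of trials under no effect and in 0.5-4.9% at the planned VO2 effect. Power was within 0.3 points.

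**The case against.** The best defence has four parts.

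- **The baseline trigger does not see outcomes.** The comparison comes before outcome analysis and uses baseline data only. This stands. A reader might infer that the method is switched after seeing results; for this rule the text does not say so.
- **Error control is intact.** A reader might also infer that the nominal 1.67% levels no longer hold. The simulations do not support that: the baseline rule is at or below nominal and the site rule stays close to it.
- **The site rule is nearly harmless.** Both branches are named, both are rank tests of the same change, and the pre-test pools the arms. It misfires in only about 5% of cases per endpoint, so a trigger that is often due to chance describes the baseline rule alone. This stands, and it makes the site rule minor.
- **Adjustment mechanics belong in a statistical analysis plan, and a categorical imbalance could go into van Elteren's test.** This stands only in part. Such a plan may supply the method, but the Protocol itself fixes the selection rule, and the rule is the defect. Van Elteren's test would not take a continuous covariate such as peak VO2 without categorising it.

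It is also fair to say that a covariate model is not the only remedy, since the sample size was justified for non-parametric tests.

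**Conclusion.** The point holds as a matter of precision and pre-specification. The baseline rule selects covariates by chance from an open list and leads to an unnamed method. It would fire in 18.5% to 64% of properly randomised trials if 4 to 20 independent variables were screened, and less often if they were correlated. Relative to adjustment fixed in advance, it gives up roughly 6 to 13 points of power for peak VO2 (82 − 76 and 88 − 75), in a trial planned at 80%. That loss assumes one covariate correlated 0.3 to 0.5 with the 12-week change; the Protocol gives no such correlation.

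The site pre-test and the conflict between its three-centre premise and recruitment at Hebrew Senior Life are minor. They should be tidied in the same edit.

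**What to change.** Delete both pre-test rules. Before unblinding, fix one analysis for all three primary endpoints, adjusted for the endpoint's baseline value and the NYHA randomisation stratum. This can be ANCOVA, or a rank-based or stratified equivalent if the non-parametric basis of Sample Size Justification is to be kept.

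Decide on site once: either always include a fixed BIDMC/other term, with Hebrew Senior Life assigned to a category explicitly, or never include one. Report baseline characteristics descriptively, without significance tests, which also removes the conflict between the two lists of baseline tests.

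The cost is wording in the Protocol and any analysis plan, with no change to data collection or sample size. If a parametric model is chosen, the 10% non-parametric efficiency allowance in Sample Size Justification must be reworded to match.
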